## Abstract

**Background:**

After total knee replacement, overall blood loss is often underestimated, although it exceeds the visible blood loss caused by bleeding into the tissues or into the joint. The use of fibrin sealants during surgery has been suggested to reduce perioperative blood loss and transfusion rates and may be beneficial for patient recovery and the postoperative function of the joint.

**Methods/Design:**

This will be a single-centre, single-blinded, randomised controlled trial with a parallel design, for which 68 patients undergoing total knee replacement will be recruited and followed up at 3, 6 and 12 months; 34 will be control patients who will receive the standard orthopaedic surgery treatment (electrocoagulation), and the other 34 will receive the same treatment plus 5 ml EVICEL™ applied during surgery and used according to the manufacturer’s instructions. The primary objective is to test the null hypothesis that the effect of EVICEL™ for controlling haemostasis and reducing postoperative blood loss in patients undergoing total knee replacement is not superior to the use of electrocoagulation alone. The secondary objective is to show that EVICEL™ reduces the need for transfusion, increases range of motion, improves clinical outcome and wound healing, and reduces the need for analgesics. The tertiary objective is to show that EVICEL™ reduces the costs of total knee replacement treatment.

**Discussion:**

So far, studies on the effect of fibrin sealants in total knee replacement have delivered inconsistent and ambivalent results, indicating that there is still a need for high-evidence studies as proposed in the presented study protocol.

**Trial registration:**

German registration number DRKS00007564; date of registration: 26 November 2014.

## Background

Implementing a new technology means using a new device in existing procedures with the global target of improving health care, thereby leading to substantial improvements in patient outcomes.

In orthopaedic surgery, especially following total hip and total knee arthroplasty, the overall blood loss is often underestimated as it exceeds the visible blood loss due to bleeding into the tissues or into the joint [1]. A large loss of blood means stress to the cardiovascular system and retards the patient’s recovery process [2]. Some patients undergoing total knee replacement (TKR) require the transfusion of allogeneic blood products in order to avoid cardiovascular complications. In addition, a postoperative haematoma may lead to an impairment of knee range of motion (ROM) [2].

Since 1972, the supportive use of fibrin sealants in selected surgical procedures has become current practice to control haemostasis and to reduce blood loss after surgery. However, the use of fibrin sealants in orthopaedic knee and hip surgery, two procedures often associated with a considerable amount of postoperative blood loss, is not considered standard.

EVICEL™ is a fibrin sealant indicated for use as a supportive treatment in surgery for the improvement of haemostasis where standard surgical techniques are insufficient. Bearing in mind that a new orthopaedic surgery guideline was published recently recommending that acetylsalicylic acid (aspirin) or clopidogrel regimens in patients undergoing orthopaedic surgery not be reduced or interrupted [3], the use of EVICEL™ in daily clinical practice might contribute to a reduction of blood loss, especially in these patients. As a consequence the use of fibrin sealants might improve healing and reduce the impaired ROM, leading to less use of analgesics after surgery, shorter hospital stays and reduced total costs of TKR treatment.

## Methods/Design

### Study design

This study will be a single-centre, parallel-design, randomised controlled trial (RCT) in which 68 patients undergoing TKR will be recruited according to the inclusion/exclusion criteria for RCTs, and treated within a 12-month period at the Department of Orthopaedic Surgery. It is registered in the German registry under number DRKS00007564. Ethical approval has been obtained from the Institutional Review Board of the Hannover Medical School under process number ‘6170 M mono’. The study will be conducted in accordance with the Helsinki Declaration.

Thirty-four (34) control patients will receive the standard orthopaedic surgery treatment (electrocoagulation). Another 34 will receive the same treatment as control patients plus 5 ml EVICEL™ applied during surgery and used according to the manufacturer’s instructions.

The main trial period is the stay in hospital for the surgery and postoperative surveillance. Follow-up examinations of all patients will be conducted 3, 6 and 12 months after surgery. With a recruitment period of 12 months and a follow-up period of 12 months, the total length of the study period is calculated to be approximately 24 months.

The study will be terminated when the necessary 34 patients per group have completed the study. Additionally, the sponsor has the right to terminate the study at any time for reasonable medical or administrative reasons. Also, the principal investigator can decide to terminate the study at any time for reasonable medical or administrative reasons.

The results manuscript will follow the advice from the CONSORT guide and its extension to cluster trials.

### Trial objectives

This randomised controlled study has three main objectives. The primary objective is to test the null hypothesis that the effect of EVICEL™ on controlling haemostasis and reducing postoperative blood loss in patients undergoing TKR is no different than with the use of standard orthopaedic surgery. The secondary objective is to show that EVICEL™ reduces the need for transfusion and increases ROM when measured 7 days after surgery and in the long term, improves wound healing and reduces the need for analgesics. In addition, two clinical outcome scores will be assessed.

The tertiary objective is to determine the influence of EVICEL™ use on the overall cost of TKR treatment.

### Primary and secondary study endpoints

The primary endpoint of this study is postoperative blood loss after TKR, measured by the difference in Hb levels at baseline (recorded in the 3 days prior to randomisation) with respect to the detected minimum in the first 7 days postoperatively and compared between the study group and the control group. During this period, blood samples will be taken regularly according to the in-house protocol, and results will be compared with control values derived from patients treated under the same conditions but without the use of EVICEL™. During the operation, all factors that affect the postoperative level of Hb will be documented.

Secondary endpoints are the need for at least one allogeneic blood transfusion or one autologous transfusion, the ROM of the operated joint, the postoperative use of analgesics, time until wound healing, clinical outcome scores, length of hospital stay, and the overall cost of the treatment.

A follow-up measurement of ROM will be conducted 3, 6 and 12 months after surgery. The ROM of the operated joint in the study and the control group will be measured using the angle of maximum flexion. Factors that might influence the ROM (for example, the use of a peripheral nerve block) will be documented and might lead to exclusion from the secondary endpoint calculation (for example, preoperative maximal flexion <90°). The need for at least one blood transfusion will be compared between the study and the control group to demonstrate whether or not EVICEL™ reduces the need for transfusions. Furthermore, it should be shown that the use of analgesics (according to the WHO pain ladder [4]) can be reduced by treatment with EVICEL™ and that the time until the wound is completely dry is shorter. In addition, it should be shown that the clinical outcome in the EVICEL™ group is better than that in the control group. Clinical outcome is assessed by two different clinical outcome scores, the clinician-completed Knee Society Score (KSS) and the patient-completed Knee Injury and Osteoarthritis Outcome Score (KOOS) [5, 6].

For the overall cost of the treatment, differences in duration of hospital stay, as well as differences in the total cost of treatment between the two groups will be compared, including the need for physiotherapy. The length of the inpatient stay depends not only on the patient’s condition but also on social and organisational factors, such as the capacity of the inpatient rehabilitation centre. Therefore, a theoretical discharge date will be defined and evaluated in addition to the actual date. The theoretical discharge date is defined as the first day on which the patient achieves the following three criteria: a dry wound without signs of infection, maximum knee flexion of at least 90° and the ability to climb stairs using crutches.

For the sake of safety, patients will be under permanent surveillance during the operation. Adverse events (AEs) and serious adverse events (SAEs) will be documented. Clinical signs of infections will be monitored daily, and blood parameters collected regularly.

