### Study procedure

On the day of admission eligible patients will be informed about the study protocol. If they agree to participate in the study and sign and date the informed consent form, the following procedure will apply (Table 1):

**Table 1 Tab1:** Schedule of events

Procedures	Baseline (within 72 h prior to procedure)	Day of surgery	Postoperative stay in hospital	3 Months after surgery ± 2 weeks	6 Months after surgery ± 2 weeks	12 Months after surgery ± 2 weeks
Inclusion/exclusion	X	X				
Randomisation		X				
Informed consent	X					
Demographics	X					
Medical history	X					
Concomitant medications including use of analgesics or peripheral nerve block	X	X	X^d^	X	X	X
Physical examination (ROM)	X		X^d^	X	X	X
Laboratory tests (virology^a^, CBC^b^, clinical chemistry^c^)	X^a–c^		X^e,b,c^			
Coagulation parameters (INR, PTT)	X					
Treatment application		X				
Intraoperative data assessment		X				
Clinical outcome score assessment (KSS/KOOS)	X		X^f^	X	X	X
Surgical site assessment			X^d^	X	X	X
Wound healing assessment			X^d^			
Assessment of patient’s mobility on crutches (stairs)			X^d^			
Adverse events		X	X^d^	X	X	X
Assessment of physiotherapy treatments after rehabilitation				X	X	X
Calculation of overall costs of TKR						X

^a^Virology: Hep B/C and HIV screening

^b^CBC: Hb, leucocytes

^c^Clinical chemistry: CRP

^d^Assessment daily during the visits (except for Sundays as for the physical examination)

^e^Assessment on days 2, 4 and 6 (+/− 1 day) and on day 7

^f^Assessment on day 7

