### Statistics

#### Sample size calculation

Statistical analysis of the published clinical evidence regarding the fibrin sealant QUIXIL, demonstrating its effects in controlling haemostasis and reducing postoperative blood loss after TKR, was used as a basis to calculate the number of patients needed for this RCT. Based on the literature [7], a sample size estimation for changes in Hb level was made with the statistical program nQuery Advisor 5.

The estimation assumes the following mean values and standard deviations (SD) of postoperative decreases in Hb [7]: 25 g/l (SD 10) (study group) and 37 g/l (SD 12) (control group). The level of significance is set at *P* = 0.05 and a two-sided *t*-test is performed with equal numbers from the two groups. With a power of 90 % and an estimated SD of 15 g/l, the required number of cases is 34 per group. For this sample size estimation we assumed that the use of additional information such as baseline Hb levels as covariates would increase the power of the test.

For a total sample size of 68, approximately 120 patients must be screened because about 40 % of the eligible patients are expected either not to meet the inclusion criteria or not to consent to participate, owing to inconvenience with the follow-up examinations; not being randomised due to intraoperative circumstances; or to drop out for other reasons. Since the primary endpoint is blood loss during the first 7 days, which is calculated using routine blood tests during the inpatient stay, no drop-outs regarding the primary endpoint should be expected after surgery (Fig. 1).

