#### Statistical methods

The statistical analysis will be carried out at the end of the study; interim analyses are not intended. However, the analysis of the primary endpoint may be carried out earlier, as soon as the data from the last patient have been assessed. For this analysis, ANCOVA for Hb level differences baseline with respect to the detected minimum in the first 7 postoperative days for both treatment groups with adjustment for baseline Hb levels will be used. If the upper limit of the two-sided 95 % confidence interval (CI) of the difference in means between EVICEL™ and standard orthopaedic surgery as estimated from the ANCOVA model is <0, the superiority of EVICEL™ will be concluded. Missing values for Hb observations will be replaced by the last observation carried forward method (LOCF). If there are no postoperative Hb values available for a particular patient, that patient will be recorded as having the largest decrease in Hb of the control group.

AEs and SAEs will be evaluated descriptively by chi-squared tests.

For the secondary endpoints, the need for at least one transfusion will be analysed by odds ratios (OR) together with 95 % CIs. The ROM and the length of hospital stay will be analysed by *t*-tests. The total cost per patient will be analysed using Wilcoxon’s signed ranks test. Time until wound healing will be tested by log rank tests.

Secondary and tertiary analyses are exploratory and will be performed descriptively.

The *P* values will be assessed descriptively and will be deemed significant when *P* <0.05.

The primary analysis will be conducted on the intention to treat (ITT) population, that is, for all randomised patients. Sensitivity analyses will be performed in the per-protocol (PP) population, including all patients who completed the study according to the protocol.

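### Range of motion is measured repeatedly but tested by t-tests, so the long-term comparison uses only attenders at a visit and can be biased if attendance depends on earlier flexion

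*Protocol article*

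**What the plan says.** All references are to the protocol article.

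- *Trial objectives*: a secondary objective is to show that EVICEL "increases ROM when measured 7 days after surgery and in the long term".
- *Primary and secondary study endpoints*: "A follow-up measurement of ROM will be conducted 3, 6 and 12 months after surgery". ROM is the angle of maximum flexion.
- *Study procedure*, Table 1: ROM is also recorded at baseline and during the hospital stay, where the footnote reads "Assessment daily during the visits (except for Sundays as for the physical examination".
- *Statistical methods*: "The ROM and the length of hospital stay will be analysed by *t*-tests". The sentence names no visit, covariate or repeated-measures structure.
- *Statistical methods*, on missing data: "Missing values for Hb observations will be replaced by the last observation carried forward method (LOCF". This rule, and the substitution for patients with no postoperative value, apply to Hb only.
- *Sample size calculation*: "no drop-outs regarding the primary endpoint should be expected after surgery". No attendance or drop-out rate is given for the 3-, 6- and 12-month visits.
- *Statistical methods*, on status: "Secondary and tertiary analyses are exploratory and will be performed descriptively".

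**The concern.** A two-sample t-test takes one value per patient. Applied at 12 months, it compares patients who came at 12 months and sets aside the flexion already recorded on those who did not. It also ignores the earlier flexion of those who did come. The comparison is safe if missing the visit is unrelated to how the knee was doing. Orthopaedic follow-up gives reasons to doubt that: a patient with a stiff knee may seek care elsewhere, and one with a good knee may see no need to return. In either case selection acts on a quantity the trial has already measured.

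At stake is the long-term half of the ROM objective, in a comparison of at most 34 patients per arm. The plan also treats its endpoints differently: Hb gets an ANCOVA with baseline, on the stated expectation that covariates raise power, while the baseline flexion it collects goes unused in the ROM test.

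**Working it through.** **The plan's own figure.** There is no sample size, SD or effect for ROM. The stated 34 per group is for Hb: difference 37 − 25 = 12 g/l, SD 15 g/l, two-sided 0.05, power 90%. The exact noncentral-t power is 0.893 at 33 and 0.902 at 34, so 34 reproduces. It does not bear on ROM.

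**What the stated test can mean.** Pooling visits in one t-test would treat several values from one knee as independent. Carrying an earlier value forward would put a recovery-phase angle in the 12-month column. The natural reading is one test per visit on those with a value.

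**Simulation inputs.** From the article: 34 per arm and the visit schedule. Assumed, because the article gives nothing:

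- Set A: SD 15 degrees, correlation 0.75 between adjacent long-term visits, true 12-month effect 6 degrees, drop-out at 6 and 12 months depending on the previous visit's flexion; 1,500 trials per scenario.
- Set B: SD 12, correlation 0.5 or 0.7 between visits, true effect 0 or 5 degrees, about 18 to 34% missing at 12 months; 4,000 trials per scenario.

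**Same dependence in both arms, set A.** Share of effect lost = (6 − mean estimate) / 6.

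| Who drops out | Missing at 12 months | t-test mean | Lost | All-visits likelihood mean |
|---|---|---|---|---|
| Poor flexion, lower rate | 17% | 5.51 | 0.49/6 = 8.2% | 6.07 |
| Poor flexion, higher rate | 25% | 5.17 | 0.83/6 = 13.8% | 6.00 |
| Good flexion, lower rate | 23% | 5.22 | 0.78/6 = 13.0% | 6.08 |
| Good flexion, higher rate | 34% | 4.95 | 1.05/6 = 17.5% | 5.99 |

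The Monte Carlo error of a mean is about 4/√1500 = 0.10 degree, so the losses are real and the likelihood means are indistinguishable from 6.

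**Same dependence, set B.** With no effect, t-test bias is between −0.01 and 0.06 degree. With a 5-degree effect it is −0.41 (correlation 0.5) and −0.56 (correlation 0.7), that is 8% and 11% of the effect. The mechanism is visible in the missing fractions: 25 to 26% in control against 18% in the better-flexing arm, so selection raises the control mean more.

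**Dependence that differs by arm.**

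- Poor flexion drives drop-out in control only, set B: bias −1.40 to −2.05 degrees.
- Dependence differing by arm, with the SD and correlation of set A and 17 to 31% missing: about 3 to 4 degrees.
- Opposite dependence in the two arms, an extreme case, set B: −2.96 to −4.69 degrees.
- The estimate using all visits stays within about 0.15 degree of the truth throughout.

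**Attendance unrelated to flexion.** Neither analysis is biased.

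**Precision without baseline, set A.** Where drop-out depends on flexion, standard errors are 3.75 to 4.25 (t-test) against 3.72 to 4.22: 1 − 3.72/3.75 = 0.8% and 1 − 4.22/4.25 = 0.7%. With random drop-out they are 3.95 to 4.07 against 3.80 to 3.86: 3.8% and 5.2%. The gain is therefore about 0 to 5%, and its upper end belongs to the setting with no bias to remove.

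**Precision with baseline.** If baseline correlates 0.5 with later flexion (assumed), the standard error with complete data falls by a factor √(1 − 0.5²) = 0.866, or 13%. This agrees with a gain of about 10 to 15%.

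**The case against.** The strongest reply is that much of this is read into one sentence. The article does not say that the tests are run separately by visit or that absent patients are left out, and an article may leave missing-data handling to a fuller document. That stands as a limit on wording: the silence on missing ROM values is not the point here. The choice of t-test is stated, however, and a model using all visits would depart from it.

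A reader might infer that the 12-month effect is biased whenever attendance depends on the knee. The documents do not support that. A mechanism shared by both arms gives no bias under no effect and attenuation otherwise, which does not flatter the product. The worst shared-mechanism shift, 1.05 degrees, is about a quarter of a standard error of roughly 4. Material bias needs a mechanism that differs by arm. Under *Randomisation/blinding*, patients and the staff collecting postoperative data are blinded, which makes that less likely. It does not exclude it, because a treatment that changes recovery can change who returns.

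Three further points stand:

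- No late drop-out rate is given. *Sample size calculation* expects patients put off by the follow-up visits to decline at the outset, so 17 to 34% missing is an assumption.
- The proposed model is not guaranteed unbiased if attendance depends on the knee's current, unrecorded state.
- No test is named for KSS or KOOS, so there is no stated method to correct for them.

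**Conclusion.** The point holds as a weakness in a stated analysis choice for a secondary, exploratory endpoint. The t-test needs attendance to be unrelated to flexion. A longitudinal model needs only that attendance depend on flexion already recorded, which is the weaker requirement.

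Under the assumed inputs, a shared mechanism costs about 8 to 17.5% of a true effect and creates none where there is none. A one-arm mechanism shifts the estimate by about 1.4 to 4 degrees, in a direction set by which arm loses its poor knees. None of these sizes can be derived from the documents. Precision is a secondary argument and becomes worthwhile only with baseline flexion in the model. The Hb conclusion is not touched. The exploratory label lowers the stakes but does not remove selection bias from an estimate the trial intends to use towards a named objective.

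**What to change.** In *Statistical methods*, replace the t-tests for ROM by one likelihood-based repeated-measures model on day 7 and 3, 6 and 12 months. Terms: arm, visit, arm-by-visit, baseline flexion and baseline-by-visit, with unstructured covariance. Include all randomised patients with at least one postoperative ROM value, and report the arm difference with its 95% confidence interval at each visit. Reconcile this set with the possible exclusions from the secondary-endpoint calculation mentioned under *Primary and secondary study endpoints*. State that the analysis assumes missed visits depend only on recorded flexion.

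The length-of-stay analysis in the same sentence is not affected. The cost is wording and a slightly more complex model; no extra patients, visits or measurements are needed, and *Trial status* says recruitment has not started.

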### Study population

A total of 68 men or nonpregnant women scheduled for primary unilateral TKR will be recruited and treated in the context of this RCT.

The inclusion criteria are as follows:Men or women aged from 55 to 70 years on the day of the operation.Patients with an indication for primary TKR on the basis of diagnosed osteoarthritis, arthritis or avascular necrosis.Patients with intact medial and lateral collateral ligaments (to be diagnosed in the preoperative examination) who are planned preoperatively to receive a Stryker Triathlon CR or Triathlon PS system prosthesis.Patients willing to participate in this RCT and who have signed the informed consent form approved by the ethics committee.

The exclusion criteria are as follows:Patients participating in any other clinical trial within 30 days before inclusion or concurrent with this study.Pregnant or nursing women.Patients tested positive for HIV, hepatitis B and C.Patients with documented or suspected hypersensitivity to any of the active substances or excipients of EVICEL™, or to bone cement or its components.Patients with acute or suspected coagulation disorders and patients with preoperative blood parameters INR >1.4 or PTT >40 s.Concomitant medication within 7 days before surgery with substances that affect haemostasis, except for low molecular weight heparins or alternatives in prophylactic dosage indicated for standard thrombosis prophylaxis.Anaemic patients showing preoperative Hb levels <11 g/dl.Patients with a deficit in extension >15° or with a maximal flexion <90°.Highly obese people (BMI >35). Patients suffering from neuromuscular or neurosensory diseases. Patients with known active tumour disease or tumour-related diseases. Patients suffering from any significant concurrent disease, illness or psychiatric disorder that would compromise their safety or compliance, or interfere with consent, study participation, follow-up or interpretation of the results. Patients receiving a prosthesis different from the Stryker Triathlon CR or Triathlon PS system owing to intraoperative circumstances (for example, bone fractures or ligament insufficiencies). Intraoperative deviation from the agreed haemostatic procedure (for example, use of the tourniquet deviating from the agreement, for example in case of surgery lasting >2 h). Patients with surgery lasting >2 h will not be randomised.

